### Primary outcome

An area under the curve approach will be undertaken to calculate QALY for each participant. Groups will be compared using regression analyses adjusted for baseline EQ-5D utility values. Analyses will be adjusted for age, gender, baseline PG-SGA category and cancer location (oesophageal, gastric, pancreatic). QALY data from individual participants will be censored at the last available measurement if the participant is lost to follow-up or withdraws.

### Secondary outcomes

Survival over the 12 month follow-up will be compared between groups using Cox proportional hazards analysis with adjustment for age, gender, baseline PG-SGA category and cancer location. Other secondary outcomes will be compared between groups using linear mixed model analyses, adjusting for baseline values of the secondary outcome and age, gender, baseline PG-SGA category and cancer location.

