### Recruitment

Eligible individuals will be identified via referrals from surgeons, ward dietitians, multidisciplinary team discussions, or screening of weekly outpatient upper gastrointestinal clinic list. Once identified, a member of the patient’s treating team (surgeon, doctor, or cancer care nurse) will be contacted to confirm eligibility and request approval to approach the patient. The recruiter will then make contact with the patient to invite them to participate. This contact will be made in person wherever possible, otherwise via phone. Once an individual gives verbal consent to participate in the study (which is the approved consent process by the Human Research Ethics Committee), baseline data will be collected. The participant’s details will then be provided to the research dietitian, who will arrange for their allocation to a group using sealed, securely stored envelopes. To optimise recruitment, the recruiter attends the weekly Multidisciplinary team meeting at a major tertiary hospital to identify potential participants. The recruiter also sends reminders to Consultants and gives updates of study progress at team meetings to remind Consultants to refer eligible people to be invited to participate in the study. Additional health services across Victoria will be contacted to be study sites to increase access to potential participants if recruitment milestones are not met.

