### Data collection

The primary method of data collection at each of the four time points (baseline, three, six and 12-months) will be via telephone or face-to-face interview with a blinded researcher. Participants will also be given the option to self-complete and return the questionnaires (described in the outcome sections) to the researcher, via email, stamped and self-addressed envelope, or in person in an inpatient or outpatient setting. These data will be entered into a coded, de-identified spreadsheet. To promote retention, participants will be reminded at each follow-up of the next planned data collection point. It will be explained why these data collection points are important to the study outcomes despite the conclusion of the active intervention period.

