### Secondary outcomes

We will use the EORTC-C30 scale as a secondary measure of health related quality of life [32]. We have included this tool along with the EQ-5D-5 L as it is a disease-specific quality of life instrument that includes items within several domains that are specific to an oncology population. This tool contains 30 items which are separated into domain scores for global health status, physical function, role function, emotional function, cognitive function, social function, fatigue, nausea and vomiting, pain, dyspnoea, insomnia, appetite loss, constipation, diarrhoea, and financial difficulties. This scale has been shown to have high construct validity, ability to differentiate populations with and without cancer, convergent validity with other health state questionnaires, and high test-retest reliability [32, 33].

Nutritional status will be measured using the Patient-Generated Subjective Global Assessment (PG-SGA) tool. This tool is widely used and has been shown to have reliable clinometric properties when used in the oncology population [34, 35]. The first section of the PG-SGA focuses on four areas and when able, is completed by the participant: weight and weight history, food intake history, nutrition impact symptoms, and activities of daily living and function. The researcher will also complete the second section which incorporates specific disease and its relation to nutritional requirements, metabolic demands, and a physical examination to determine loss of subcutaneous fat and muscle wasting if face-to-face data collection is possible.

Other secondary outcome measures include survival over the 12 month follow up period and changes in self-reported body weight. Where possible (if face-to-face data collection is possible) we will measure waist circumference and hand grip strength using a hand dynamometer (Jamar Digital Hand Dynamometer, Lafayette, Indiana, USA) to support our data relating to changes in nutritional status. For the same reason, tissue density from CT scans taken as routine care pre and 3 month post treatment will be analyzed at the 3rd lumbar vertebra to determine body composition (skeletal muscle, visceral and subcutaneous fat) using Slice-O-Matic software (v.5.0; Tomovision, Montreal, Quebec, Canada).

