### Data analysis

The advisory committee will review data cleaning. A mixed methods approach to analysis will comprise a clinical effectiveness study and a concurrent and cost-utility economic evaluation. The primary outcome will be health-related quality of life, converted to quality-adjusted life years lived. Multiple imputation will be used to replace missing individual data points for conducting comparisons in mean QALYs per participant between groups.

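### Waist and grip strength: with baseline as a covariate, participants measured at follow-up but not at baseline drop out of the comparison, which costs precision

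*Protocol article*

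**What the plan says.** The Secondary outcomes paragraph of the analysis part of the protocol article sets Cox regression for survival and one model for everything else: "Other secondary outcomes will be compared between groups using linear mixed model analyses, adjusting for baseline values of the secondary outcome", followed by age, gender, baseline PG-SGA category and cancer location. The outcome's own baseline value stands in the same adjustment list as age and gender, so it is a covariate.

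The earlier Secondary outcomes section, which defines the measures, makes two of them conditional on the mode of contact: "Where possible (if face-to-face data collection is possible) we will measure waist circumference and hand grip strength using a hand dynamometer".

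The mode is not fixed at any visit, and baseline is named among the visits: "The primary method of data collection at each of the four time points (baseline, three, six and 12-months) will be via telephone or face-to-face interview". The Recruitment section says of the first approach: "This contact will be made in person wherever possible, otherwise via phone". Baseline data follow verbal consent, and allocation by envelope comes after that.

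The only method given for missing data is in the opening paragraph of Data analysis: "Multiple imputation will be used to replace missing individual data points for conducting comparisons in mean QALYs per participant between groups".

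**The concern.** The measurement rule and the analysis rule do not fit together. Because the mode may differ from visit to visit, a participant can have a telephone baseline and be seen in person later. That person then has follow-up waist or grip values but no baseline value.

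A likelihood-based mixed model copes with missing responses, but it cannot use a row in which a covariate is missing. Every follow-up row of such a participant is lost, however many there are.

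At stake are measurements already taken from ill patients in a trial of 37 per group. The article wants waist and grip to back up its data on change in nutritional status, much of which comes from the participant (self-reported weight, first section of the PG-SGA).

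**Working it through.** **The plan's own figure.** The article gives no figure for waist or grip. Its only sample-size figure is for QALYs. Taking alpha 0.05 as two-sided (the article does not say), 80% power and a standardised difference of 0.70, n per group = 2 × (1.960 + 0.842)² / 0.70² ≈ 32.0, rounded up to 33. Allowing 10% drop-out, 33 / 0.9 = 36.7, rounded up to 37. The figure reproduces and is not in dispute. It serves here only to set the total at 3 × 37 = 111.

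**Step 1: who is kept.** Take 111 participants, all measured at three follow-ups, with a given share lacking a baseline value. Both the full follow-up and the shares are assumptions. Building the design with group, time and baseline as terms and counting usable participants gives:

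| Share without baseline | Kept, baseline as covariate | Kept, baseline as a response |
|---|---|---|
| 10% | 100 | 111 |
| 30% | 78 | 111 |
| 50% | 55 | 111 |
| 70% | 33 | 111 |

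The proportion lost equals the share without a baseline.

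**Step 2: what the loss is worth.** Head count overstates it, because a participant without a baseline carries less information. Consider one follow-up visit. Let p be the share of those measured at follow-up who lack a baseline, r the baseline to follow-up correlation, σ² the outcome variance and N the number measured.

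- Information from those with a baseline: N(1 − p) / [σ²(1 − r²)]
- Information from those without: Np / σ²
- Ratio, everyone against those with a baseline only: 1 + [p / (1 − p)] × (1 − r²)
- Reduction in standard error: 1 − 1 / √ratio

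With assumed ranges p = 0.1 to 0.4 and r = 0.5 to 0.85:

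| p | r | Ratio | Cut in standard error |
|---|---|---|---|
| 0.1 | 0.85 | 1 + 0.111 × 0.2775 = 1.031 | 1.5% |
| 0.3 | 0.7 | 1 + 0.429 × 0.51 = 1.219 | 9.4% |
| 0.4 | 0.85 | 1 + 0.667 × 0.2775 = 1.185 | 8.1% |
| 0.4 | 0.5 | 1 + 0.667 × 0.75 = 1.500 | 18.4% |

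**Step 3: does the exclusion depend on arm?** The Recruitment section has the order consent, baseline data, allocation. Whether a baseline waist or grip value exists is thus settled before the arm is known. Excluding on it leaves a randomised comparison in a narrower group of people.

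**The case against.** The best objection is that the article nowhere says these participants are dropped. It says only that the models adjust for baseline. Naming imputation for QALYs does not forbid it elsewhere, and a SAP that is not shown might impute the baseline or model it as a response. This is fair as far as it goes: the exclusion is a consequence of the model as written, not a stated rule. But the choice of model is stated, and it suits poorly a measurement rule that makes missing baselines foreseeable. A SAP could repair this only by adding to or departing from that choice.

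Second, the size is assumed. Recruitment contact is to be in person wherever possible, so baseline may be the visit most often held face-to-face and the share affected may be small. This stands. The 18% figure also needs the worst corner of both ranges.

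Third, baseline-adjusted mixed models are a standard and valid choice, and with complete data the alternative gives essentially the same estimate. This stands too. The gain is in efficiency and coverage, on two measures that the article already treats as supportive.

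A reader might go further and infer that the arm comparison is biased, because in-person contact at follow-up could depend on the intervention. The stated mechanism does not support that. Exclusion for a missing baseline precedes allocation. Selection through missing follow-up measurements is a separate matter, which baseline adjustment does not cause. Nor does the Data collection section's mention of inpatient or outpatient settings say where waist or grip is measured; it concerns the return of self-completed questionnaires.

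A reader might also take waist and grip to be the only measures besides CT that do not rest on participant report. They are not: deaths are extracted from a registry, and the PG-SGA includes a physical examination by the researcher when contact is face-to-face.

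**Conclusion.** The point holds as a matter of precision and representativeness. Under the model as written, anyone with follow-up but no baseline waist or grip value contributes nothing to those comparisons. If 10% to 40% of those measured at follow-up lack a baseline and the correlation is 0.5 to 0.85, retaining them would lower the standard error by roughly 2% to 18%, and by about 9% at 30% and 0.7. The article gives neither the share nor the correlation, so the range illustrates the size and does not estimate it.

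The mechanism does not by itself bias the contrast between arms. It touches two supportive measures and leaves the primary QALY analysis as it is. It is worth correcting because the correction costs almost nothing.

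**What to change.** For waist circumference and grip strength, replace adjustment for baseline as a covariate with a constrained longitudinal mixed model:

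- baseline is one of the repeated responses, alongside 3, 6 and 12 months;
- the baseline mean is common to the three groups, as randomisation justifies;
- group-by-time terms give the contrasts of each intervention group with control;
- age, gender, baseline PG-SGA category and cancer location stay as covariates.

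Everyone with at least one measurement then enters the model. Report the number measured in person by arm and visit, because the model does not remove selection from follow-up measurements that were never taken. Present the two outcomes as supportive estimates with confidence intervals.

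The cost is a sentence or two of analysis wording and a slightly more complex model. No new data, visits or participants are needed.

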### Economic evaluation analysis

A trial-based, cost-utility analysis will be undertaken to understand what the cost per quality adjusted life year gained is of each intervention group relative to the control group. This economic evaluation will be conducted from the societal perspective over a 12 month follow-up horizon. It will take the form of an incremental cost-utility (cost per quality-adjusted life year gained) analysis. Bootstrap replications of the trial dataset will be used to generate a 95% confidence ellipse surrounding the cost-utility point estimate, and to inform cost-utility acceptability curve analyses. One-way sensitivity analyses will be used to investigate the stability of the main trial finding to variation in key clinical and economic inputs. Exploratory analyses will be undertaken to identify potential intervention interaction effects with age, confidence to use and pre-existing use of iPad/smart phone.

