There is need to generate more conclusive evidence as to whether early nutrition intervention is effective and feasible in this population. It is also important to determine whether technology-enabled mechanisms for delivery of early nutrition intervention are as effective as telephone-based delivery approaches. We propose a three group randomised controlled trial to address these needs. Specifically, we seek to determine whether an internet-enabled mobile application (App) or intensive telephone counselling intervention can be used to effectively (and cost-effectively) deliver the early nutrition counselling intervention to people with gastric, oesophageal or pancreatic cancer in addition to the usual nutritional care they may later receive. It is hypothesised that participants allocated to receive the early and intensive pre-hospital dietetic service will have more quality-adjusted life years lived compared with control participants.

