### Intervention

The intervention is provided in addition to usual care. In this study the same intervention will be delivered by two different modes, via telephone or via mHealth (described in sections below) (Fig. 1). The intervention period will be 18 weeks, commencing as early as possible from the time of diagnosis. Following an initial assessment, weekly or fortnightly reviews will continue throughout the intervention period, as agreed by the dietitian and the participant. Participants who are in hospital at the time of a planned dietetic phone review will not receive their intervention that week, as it is assumed that whilst in hospital they will be receiving dietetic input as required, as part of ‘usual care.’ The intervention will re-commence once the participant has been discharged home, and the intervention timeline will not be suspended.

The intervention will be delivered by a research dietitian with experience in provision of clinical care to this population. The intervention will be delivered according to a Standard Operating Procedure that specifies a list of behaviour change techniques that can be employed through both of the intervention arms (Table 1). The behaviour change techniques specified are drawn from the Behaviour Change Technique Taxonomy (v1) [24]. The dietitian will set goals and instructions on how to perform the behaviour with the participant and provide tailored nutritional recommendations based on the participant’s history and nutrition impact symptoms. In the subsequent review session reviewing of goals will feature and other secondary behaviour techniques can be used if the initial behaviour techniques are not successful (Table 1).

**Table 1 Tab1:** Example of behaviour change techniques [24] used at the initial assessment (t_1_) and subsequent reviews (t_2_-t_18_)

	Behaviour change technique	Definition [24]	Example	Classification^a^
Initial assessment (t_1_)	Goal setting (behaviour)	Set or agree on a goal defined in terms of the behaviour to be achieved	Set the goal of eating 5 pieces of fruit per day	Routinely Used
	Goal setting (outcome)	Set or agree on a goal defined in terms of a positive outcome of wanted behaviour	Set a weight gain goal (e.g. 0.5 kg over one week) as an outcome of changed eating patterns	Supplementary

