### Telephone group

Participants randomised to the telephone group will receive regular phone contact from the research dietitian. An initial assessment will be completed over the phone, with subsequent weekly or fortnightly phone reviews depending on the therapist perception of participant’s needs. Any contact in addition to these scheduled reviews is permissible and will be documented, for example if the participant calls the dietitian with an urgent nutritional issue. Total time spent in conversation with participants will be documented, to allow for a cost analysis between intervention groups (see below).

If a participant is unavailable for a scheduled phone review, the research dietitian will attempt to arrange a more convenient time for the participant. In the event of a second instance that a participant is unavailable in the same week, then no intervention will occur that week. This will be documented, as will the reason for the participant’s unavailability (if known).

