A key limitation in this study is the length of follow-up we are able to provide being insufficient to generate sufficient statistical power to examine the impact of these interventions on survival. Ideally, this length of follow-up would be extended up to a 5 year period so that the effects of this intervention on both survival and quality-adjusted life years lived could be observed. Previous research has indicated that survival rates in these populations are likely to be below 20% at this time [51], thus this research has great potential to demonstrate benefits on this outcome (if they exist) if further resources can be secured to extend the follow-up of participants in this study out to 5 years.

A limitation of this research related to the interventions being tested is that we are not pursuing a blended online and telephone based intervention delivery approach. The investigators felt it more important to determine whether a technology-based intervention could stand alone as a service delivery model in this population. Asynchronous online interactions with a health professional are attractive as they allow health professionals to be maximally efficient with their work time. There is no time wasted trying to track patients down so that they can talk to them on the phone or speak in person. Instead, feedback from health professionals can be provided at a time convenient to them, making it easier to interact with a greater number of patients in a busy day. Conversely, the strength of the relationship between patient and health professional may be weakened without the direct, synchronous interaction. If there are limitations with this approach, then these limitations need to become apparent through this research.

It is anticipated that successful results from this study could rapidly impact people newly diagnosed with cancers of the upper gastrointestinal tract. Scalable service is possible with either of these service delivery models. The patient-centred approach (delivered at home, at a time convenient to the patient) is relevant to current health service provision and challenges the current reactive delivery model of care.

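### The cost-utility analysis is defined for each mode against control and commits to no joint cost-and-QALY comparison of telephone with mHealth, although they are alternative ways of delivering one intervention

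*Protocol article*

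**What the plan says.** The comparator is fixed in the protocol article under Economic evaluation analysis, where the aim is to learn "what the cost per quality adjusted life year gained is of each intervention group relative to the control group". On form, the section says: "It will take the form of an incremental cost-utility (cost per quality-adjusted life year gained) analysis". On uncertainty, bootstrap replications are to "generate a 95% confidence ellipse surrounding the cost-utility point estimate, and to inform cost-utility acceptability curve analyses". The section does not mention a telephone-versus-mHealth increment, an ordering of the three options, a check for dominance or a net-benefit comparison across arms.

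Other sections bear on how the modes relate:

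- Background asks whether the App or telephone counselling "can be used to effectively (and cost-effectively) deliver the early nutrition counselling intervention", on top of usual nutritional care. It separately calls it important to learn whether technology-enabled delivery matches telephone delivery in effectiveness.
- Intervention says that "the same intervention will be delivered by two different modes, via telephone or via mHealth".
- Discussion says "we are not pursuing a blended online and telephone based intervention delivery approach", and on roll-out: "Scalable service is possible with either of these service delivery models".
- Telephone group records conversation time "to allow for a cost analysis between intervention groups". Adherence gives a matching purpose for contact time in the mHealth arm.
- Primary outcome, under Data analysis, says groups will be compared on QALYs by regression, without naming which pairs of groups.

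**The concern.** A health service reading the results has at least three options: usual care alone, usual care plus telephone, or usual care plus mHealth. When options are alternatives, the decision depends on what each step up in cost buys over the next cheaper option that is still worth considering. A ratio against a common control averages over the whole distance from control. It can stay moderate while the last step is very expensive, or while the option costs more and yields less than its rival.

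The article gives reasons to expect the modes to differ on both axes. The mHealth arm may need tablets and connectivity (section mHealth group). The Discussion expects asynchronous contact to save clinician time, but allows that it may weaken the relationship with the patient. Only cost and QALYs taken together can settle that trade-off. A separate cost-effectiveness paper meant to inform policymakers is planned (Dissemination), and the choice of mode is a question its readers will bring.

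**Working it through.** **1. The article's only design figure.** Under Sample size calculation: standardised difference 0.70, alpha 0.05 (two-sided assumed), power 80%, each comparison with control. n per group = 2 × (1.960 + 0.842)² / 0.70² = 15.70 / 0.49 = 32.04, rounded up to 33. The t-test version gives 33.02, with power 0.7997 at 33. The stated 33 reproduces, and 37 recruited corresponds to 1 − 33/37 = 10.8% dropout. Nothing here disputes that figure. It matters because it shows which comparison the trial was sized for.

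**2. What is planned between the modes.**

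| Section | Cost | QALYs | Telephone vs mHealth |
|---|---|---|---|
| Telephone group; Adherence | contact time | no | yes |
| Primary outcome (Data analysis) | no | yes | not specified |
| Economic evaluation analysis | yes | yes | not stated; control is the comparator |

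No row commits to cost and QALYs together between modes.

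**3. What the omission can hide.** Every cost, QALY gain and threshold below is an assumption, in arbitrary currency units. Telephone is called A and mHealth B; the labels can be swapped without changing the logic. ICER = ΔC/ΔQ. Net monetary benefit over control: NMB = λ × ΔQ − ΔC.

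*Case (a), poor value.* A: +1,000 and +0.05. B: +2,400 and +0.06.

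- A vs control: 1,000/0.05 = 20,000.
- B vs control: 2,400/0.06 = 40,000.
- B vs A: (2,400 − 1,000)/(0.06 − 0.05) = 1,400/0.01 = 140,000.

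*Case (b), dominated.* A: +1,000 and +0.05. B: +1,500 and +0.04.

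- A vs control: 20,000.
- B vs control: 1,500/0.04 = 37,500.
- B vs A: 500 more cost and 0.01 fewer QALYs, so B is dominated.

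NMB over a range of thresholds:

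| λ | (a) A | (a) B | (b) A | (b) B |
|---|---|---|---|---|
| 30,000 | 500 | −600 | 500 | −300 |
| 50,000 | 1,500 | 600 | 1,500 | 500 |
| 100,000 | 4,000 | 3,600 | 4,000 | 2,500 |
| 150,000 | 6,500 | 6,600 | 6,500 | 4,500 |

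In case (a), for any λ between 40,000 and 140,000, both modes look acceptable against control while A has the higher net benefit. Below 40,000, B already fails against control. Above 140,000, B is the better choice. In case (b), B looks acceptable against control for any λ above 37,500, but A is better at every threshold shown.

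**4. Precision of a between-mode comparison.** With 33 per arm, the standard error of an unadjusted standardised difference is about √(2/33) = 0.246, so a 95% interval is about ±1.96 × 0.246 = ±0.48 SD. With 37 per arm it is ±1.96 × √(2/37) = ±0.46 SD. The between-mode QALY difference will therefore be imprecise unless it is large.

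**The case against.** The case for leaving the plan alone has real parts.

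- *Control is a legitimate comparator.* Usual care is current practice, and the hypothesis and sample size are both set against it. The between-mode question in the Background is worded about effectiveness, not cost. This stands, and it is why the ratios against control should remain.
- *Detail may sit in an analysis plan that is not shown.* The words about an incremental analysis and acceptability curves do not exclude a three-option analysis. This stands in part: the article does not forbid one. But the comparator is positively stated, so this is a stated choice that falls short, not simply missing detail.
- *The modes are not wholly uncompared.* Contact-time costs are compared between them, and the QALY regression may cover the same pair. This stands, so a reader would be wrong to infer that no between-mode comparison of any kind is planned. Only the joint comparison is uncommitted.
- *Mutual exclusivity is inferred.* The article rules out a blended intervention in the trial, but does not say that a service must fund only one mode. Its exploratory interactions with age and device use are compatible with offering different modes to different patients. This stands as a limit. Even so, wherever a patient could receive either mode, the relative value of the two is the relevant question.
- *The increment can be recovered by subtraction.* With a shared control, point differences between modes follow if the cost and QALY differences are reported. They do not follow from the ratios alone, and the between-mode uncertainty needs joint bootstrap draws.

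A reader might go further and infer that the plan will endorse a poor-value mode. The article does not support that: it states no threshold and no adoption rule, and gives no figures from which a wrong conclusion could be shown.

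**Conclusion.** The point holds as a gap in a secondary analysis. The cost-utility comparison is fixed against control, and nothing commits to comparing the two modes on cost and QALYs together, although they are presented as alternative stand-alone deliveries of the same intervention. The consequence is possible, not certain. Under the assumed figures, two modes at 20,000 and 40,000 per QALY against control are separated by a step of 140,000 per QALY, and in the second case one mode is strictly dominated while still at 37,500 against control. These numbers show the mechanism and say nothing about which mode will be dearer or better.

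It would be too strong to conclude that the ratios against control are wrong or should be displaced. They answer the question that the trial was hypothesised and sized on, and for the cheapest non-dominated mode that costs more than control, the ratio against control is also the sequential one, provided that mode is not extendedly dominated. They are incomplete for choosing between modes.

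**What to change.** Keep the planned ratios of each mode against control. Add to Economic evaluation analysis, or to the analysis plan:

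1. A fully incremental analysis of the three arms: order them by mean cost, identify dominated and extendedly dominated options, and report sequential ICERs for the rest.
2. From the same bootstrap, with all three arms resampled jointly in each replication, net monetary benefit per arm and a three-option acceptability curve (probability that each arm has the highest net benefit) over a stated range of thresholds.
3. A statement that the between-mode result is estimation with its uncertainty, because the trial is sized only for comparisons with control.

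The cost is some wording and analysis code. No new data, participants or follow-up are needed, and the primary analysis does not change. The downside is a little more analysis and a between-mode estimate that will probably be imprecise. Net benefit and the acceptability curve display that imprecision better than a ratio, which becomes unstable when the QALY difference is small.
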